#### Inclusion criteria

• Written informed consent

• Age: between 18 and 75 years

• Chronic tinnitus since at least 6 month, but not more than 5 years.

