### Outcome measures

The primary efficacy measure in the present study is the change of the tinnitus distress as measured by the TQ [45] after 4 weeks of cTBS. The TQ [45]), originally developed by Hallam et al. [49], is the most widely used, well validated and reliable inventory [50] to quantify tinnitus ditress available in German language [30,32,34,41,51-58]. It comprises 52 multi-scaled items in order to assess emotional and cognitive handicaps, penetrance of the tinnitus, hearing problems, sleep disturbances, and somatic discomfort. The TQ was used in pharmacological, behavioural and TMS studies. Pharmacological studies did not yield therapeutic effects [58,59]. Behavioural therapy yield effect sizes between 6 and 28% on the TQ [60,61]. Pilot rTMS studies reported effects sizes between 5 and 25% [34,41,52].

Secondary efficacy variables are tinnitus change [46] and the changes in BDI [47] and in the VAS for tinnitus loudness and tinnitus annoyance [46,62].

Changes regarding psychopathology will be measured using the SCL-90R [48]. Feasibility of the study will be assessed and reported together with the results.

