### Sample size calculation

Effect size and dispersion were taken from our last study of TMS against tinnitus [34]. The ratios of tinnitus distress score after treatment to tinnitus distress score at baseline are assumed to follow normal distributions with standard deviation 0.18 after taking logarithms. A relevant effect size of 0.19 logarithmic units would arise from the ratio of geometric mean scores of 80% of baseline after efficacious stimulation to 97% after sham stimulation. All three pairwise group comparisons will be conducted. Therefore the probabilities of the errors of first and second kind are Bonferroni-adjusted to significance level 0.017 and power 0.93 locally to ensure multiple level 0.05 and multiple power 0.8. Consequently the planned number of patients to be included in the study is 48, i. e. 16 in each arm. A closed testing procedure preserves the multiple significance level and power while treatments are compared at different points in time.

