### Data analysis

The geometric mean tinnitus score (TQ) in percent baseline will be compared between the three groups after the full treatment course of 4 weeks after the first stimulation, after 6 weeks, as well as 28 and 56 weeks after the first cTBS treatment in that prespecified order, as we expect effects sizes to have that order. If one group comparison is not statistically significant, the following comparisons are rated as not significant too. The confidence intervals for ratios of geometric means of tinnitus scores at 4 and 6 weeks will be computed from an analysis of variance (ANOVA) with factors *group *(SAC, TAC, PLC) and *time *(4 and 6 weeks) and the *group*time *interaction. Further ANOVAs of TQ with the between subject factor *group *will be carried out after 8, 28, and 56 weeks after the first treatment. Their residual variances are expected to differ. The longitudinal course of the stimulation effect will be described using all TQ measurements, including measurements at 2 and 16 weeks. Secondary efficacy measures will be analysed similarly. Only the tinnitus change cannot be divided by a baseline value and will be analysed by ordinal logistic regression as it is ordinal. The daily measurements on visual analog scales will be shown in diagrams. Confidence interval computations will assume normality of logit-transformed VAS. The routinely sampled safety data will all be plotted for each patient and will be used to quantify intensity and duration of adverse effects should such occur. Data analysis will be performed in the Department of Medical Biometry of University Hospital of Tübingen using JMP 7.0 (SAS Institute Inc.) after imputation with SPSS 17.0 (SPSS Inc.).

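### The plan's rule has BDI analysed as a log ratio to baseline, which is undefined at a score of 0 and unstable at low scores

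*Protocol article*

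**What the plan says.** In the protocol article, Data analysis sets the primary method: "The geometric mean tinnitus score (TQ) in percent baseline will be compared between the three groups". Sample size calculation gives the model behind it: post-treatment to baseline ratios of the distress score "are assumed to follow normal distributions with standard deviation 0.18 after taking logarithms". Data analysis then extends the method: "Secondary efficacy measures will be analysed similarly". One exception follows: "Only the tinnitus change cannot be divided by a baseline value and will be analysed by ordinal logistic regression as it is ordinal".

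Outcome measures lists the secondary efficacy variables as tinnitus change, change in BDI, and change in the VAS for loudness and annoyance. The VAS gets a further sentence in Data analysis: "Confidence interval computations will assume normality of logit-transformed VAS".

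Two other places bear on the point. Inclusion criteria asks for consent, an age range and a tinnitus duration ("Chronic tinnitus since at least 6 month, but not more than 5 years"), with no minimum on BDI, VAS or TQ. The imputation rule in Data sets covers missing observations. An observed zero is not missing.

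**The concern.** A ratio to baseline suits a score that stays well above zero. The BDI is a depression inventory given here to patients selected for tinnitus, and entry does not require depressive symptoms. Some may score 0 or close to it at baseline, and others may reach 0 after treatment. The stated rule gives no usable value for a zero, and for scores just above zero it turns a change of a point or two into a very large log ratio.

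If this is noticed only at analysis, someone must choose a repair with the data in view. With 16 patients per arm, that choice can decide what the BDI comparison shows.

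**Working it through.** The plan gives no figure for this point, so there is none to reproduce. The check asks where the prescribed quantity exists and how it behaves near the edge.

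**Inputs**
- Analysis quantity: log(y/b), with y the follow-up and b the baseline score (Data analysis, Sample size calculation).
- 48 patients, 16 per arm (Sample size calculation).
- Assumption: the lowest BDI total is 0. The article does not state the range.
- Assumption: the share p of patients with a BDI of 0 at a given visit is 2% to 20%. The article gives no figure.

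**1. Where the quantity exists**
- y/b needs b > 0. With b = 0 it is undefined.
- log(y/b) also needs y > 0. With y = 0 it is minus infinity, and the arm's geometric mean becomes 0 whatever the other patients score.

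**2. Chance of meeting a zero**
P(at least one among 48) = 1 − (1 − p)^48.

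| Assumed p | Expected number, 48p | P(at least one) |
|---|---|---|
| 2% | 0.96 | 62% |
| 5% | 2.4 | 91% |
| 10% | 4.8 | 99% |
| 20% | 9.6 | >99.9% |

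**3. Low scores without a zero**
- BDI 1 to 3: ln(3/1) = +1.10.
- BDI 3 to 1: ln(1/3) = −1.10.
- BDI 11 to 13, the same two points: ln(13/11) = +0.17.

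The same change in points counts 1.10/0.17, or about 6.5 times, as much at the bottom of the scale.

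**4. Adding a constant**
Take an arm of 16. Fifteen patients have ratio 0.80, held fixed for simplicity, and one goes from 10 to 0. With constant c, that patient contributes ln(c/(10 + c)), and the arm's geometric mean ratio is exp{[15·ln(0.80) + ln(c/(10 + c))]/16}, where 15·ln(0.80) = −3.347.

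| c | ln(c/(10 + c)) | Geometric mean ratio | Log-scale SD |
|---|---|---|---|
| 0.01 | −6.909 | 0.53 | 1.67 |
| 0.1 | −4.615 | 0.61 | 1.10 |
| 0.5 | −3.045 | 0.67 | 0.71 |
| 1 | −2.398 | 0.70 | 0.54 |

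The estimate and its spread both depend on a constant that the plan does not fix. On the raw scale the same patient contributes a change of −10 points, which is 10/16 = 0.625 points of the arm mean, and no constant is needed.

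**The case against.** **The exempting sentence may be about something else.** Table 1 schedules the VAS for change only at V11 and V21, with no baseline entry, while BDI has one at V1. The sentence can therefore mean simply that tinnitus change has no baseline to divide by. On that reading it is true, and it gives a sound reason for ordinal regression. This stands: a reader might take the sentence as a false claim that every BDI value can be a divisor, but the text does not force that. What remains is its effect. BDI is left under the general rule, and the rule fails at zero.

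**A journal article is condensed.** Analysing measures similarly need not mean identically, and handling of boundary values commonly sits in a fuller document. This carries weight for the VAS. It carries less for BDI, where the only method the article states is one that breaks at zero.

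**Zeros may be rare.** Background lists depression among the most common comorbidities of tinnitus, so many patients may score well above 0. That is fair, and the frequency is unknown. But no entry criterion keeps scores off the floor.

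**The VAS.** A reader might infer that percent of baseline and logit contradict each other. The article does not establish this: the specific logit sentence can replace the general rule. A logit is a recognised choice for a bounded scale and needs only a convention for its ends.

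**Loss of patients.** A reader might also infer that patients with zeros will be dropped by the software. Nothing in the article says so. Exclusion, recoding to missing followed by imputation, or an added constant are all possible.

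**Conclusion.** The point holds for BDI. Followed as written, the plan prescribes a log ratio to baseline that is undefined for a zero baseline, minus infinity for a zero at follow-up, and unstable at low scores. It rests on two assumptions: that the BDI floor is 0, and that some patients score at or near it. How many do is not known. The range from 0.53 to 0.70 is a constructed illustration and no forecast for this trial.

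The planning SD of 0.18 should not be used to judge the size of BDI changes. It belongs to the log ratio of the tinnitus distress score, and no variability is given for BDI.

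For the VAS the point is a minor clarification. The primary TQ analysis is not affected by this point. The change is worth making because it costs almost nothing and removes a choice that would otherwise be made after the data are seen.

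**What to change.** **BDI.** State that BDI is analysed at each planned time point by ANCOVA on the raw score, with group as factor and baseline BDI as covariate. Name BDI as an exception to the percent-of-baseline rule.

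**Tinnitus change.** Keep ordinal logistic regression, and give the reason explicitly: the measure has no baseline value.

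**VAS (clarification).** State that loudness and annoyance are analysed on the logit scale in place of the ratio, with baseline on the same scale as covariate and an end-of-scale adjustment fixed in advance. The adjustment matters: on an assumed 0 to 100 line, moving a zero to 0.1, 0.5, 1 or 2 gives logits of −6.9, −5.3, −4.6 or −3.9.

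**Cost.** Wording only. Table 1 already schedules BDI and the loudness VAS at baseline and follow-up, so no patients, visits or data are added. The downside is that the BDI effect is reported in points and not as a percentage of baseline, so it no longer shares a scale with the TQ result.

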### Objectives

We hypothesize that compared to sham stimulation cTBS can induce a distinctive attenuation of tinnitus distress and loudness and thus be of therapeutic value. Further aims of the study are:

• To compare the effect of cTBS on the secondary auditory cortex with its effect on the temporoparietal association cortex.

• Assessment of safety in terms of impairment in audiologic and speech-audiometric measures as well as the documentation of other unwanted side effects.

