### Baseline assessments

The detailed time course and plan of the study is displayed in Table 1.

**Table 1 T1:** Time course of the study

Investigation	Screening	Baseline	Treatment				Follow-Up				
			
			2 weeks		2 weeks		11 months				
Visit #	V0	V1	V2-10	V11	V12-20	V21	V22	V23	V24	V25	V26

informed consent	×										

demograph. data	×										

inclusion/exclusion criteria	×										

randomization		×									

ENT investigation/tinnitus localization		×									

audiogram/speech audiometry		×		×		×					

STI		×									

cTBS treatment SAC, TAC, PLC			×	×	×	×					

documentation of side effects			×	×	×	×					

TQ		×		×		x *	×	×	×	×	×

VAS (distress, loudness)		×	×	×	×	×	×	×	×	×	×

VAS (change)				×		×					

SCL-90R		×		×		×	×	×	×	×	×

BDI		×		×		×	×	×	×	×	×

*primary outcome measure

• Ear Nose and Throat (ENT) examination and audiological assessment including

- Standard pure tone audiometry

- Speech audiometry in quiet (mono- and multi-syllables, "Freiburger speech test")

- Hearing in noise test ("Oldenburger sentence test") [42]

- Audiological tinnitus matching

• Structered Tinnitus Interview (STI) [43]

• Tinnitus Questionnaire (TQ) [44,45]

• Visual Analogue Scales (VAS) for tinnitus loudness and annoyance [46]

• Beck Depression Inventory (BDI) [47]

• Symptom checklist 90-revised (SCL-90R) [48].

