### Safety

Safety measures are pure tone and speech audiometry as well as speech understanding in noise tests (at Baseline, after 2 weeks of treatment and after the end of the treatment). Adverse events are assessed daily and documented according to the GCP guidelines. Safety and adverse events will be reported together with the results. The occurence of possible adverse effects will be reported in a case report form and handled in compliance with GCP. Study monitoring is provided by CenTrial (Tübingen, Germany).

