### Treatment

After screening, written informed consent, physical ENT examination and audiological assessments, patients will be assigned to one of the real (SAC, TAC) or sham (PLC) treatment groups. TMS will be applied using a Magstim Super Rapid (The Magstim Company Ltd, Whitland, UK) with a figure-eight coil (diameter of each winding: 70 mm, biphasic stimulus of 250 μs, peak magnetic field: 2T). The individual motor threshold (AMT) will be assessed at the beginning of the first treatment session. AMT is defined as minimum stimulation intensity required to induce a motor evoked potential (MEP) of more than 200 μV on at least 5 out of 10 trials from the contralateral abductor pollicis brevis muscle (APB) while maintaining a voluntary contraction of about 20% of maximum [39]. Stimulation (cTBS) intensity is 80% AMT and will be applied to each side for 40 s in alternating order. Fifteen minutes after the first two trains, a second pair of cTBS will be applied (a total of 2400 stimuli per day). Patients receive cTBS treatment each working day for 4 weeks.

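### The plan promises the duration of adverse effects, but scheduled safety recording stops at the last treatment visit, so any effect still present then has only a minimum duration

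*Protocol article*

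**What the plan says.** Safety is a named aim of the trial. The Objectives list "Assessment of safety in terms of impairment in audiologic and speech-audiometric measures as well as the documentation of other unwanted side effects". The Data analysis section then states what will be done with the data: the routinely sampled safety data are to be plotted patient by patient and "will be used to quantify intensity and duration of adverse effects should such occur".

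The collection schedule appears in three places in the protocol article.

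- **Table 1 (Baseline assessments).** The row "documentation of side effects" is marked at V2-10, V11, V12-20 and V21. These are the same columns as the row "cTBS treatment SAC, TAC, PLC". It is blank at V22 to V26. Audiogram and speech audiometry are marked at V1, V11 and V21 only.
- **Safety.** Audiometric measures are taken "at Baseline, after 2 weeks of treatment and after the end of the treatment". For other events: "Adverse events are assessed daily and documented according to the GCP guidelines". Adverse effects go into a case report form and are handled under GCP.
- **Follow-up assessments.** The visits at weeks 6, 8, 16, 28 and 56 collect TQ, VAS and BDI. Table 1 adds the SCL-90R.

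**The concern.** The article states an analysis (duration of adverse effects) and names its source (routinely sampled safety data). It also gives an explicit schedule for those data, which ends on the day of the last stimulation. The two agree for effects that come and go during treatment. They do not agree for effects present at the end of the course or arising after it.

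The trial applies a four-week course, whereas the Background describes earlier repeated low-frequency rTMS of up to 2 weeks. The Discussion says a larger efficacy study will be designed from the results. Benefit is followed to week 56. On the written schedule, a side effect seen at the last session could not be classed as brief or lasting, and a hearing change seen there could not be classed as reversible or not.

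**Working it through.** No sample size or power figure is involved, and the plan gives no figure of its own to reproduce. The check compares the schedule with the stated analysis.

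**1. Where V21 falls.** The Treatment section says: "Patients receive cTBS treatment each working day for 4 weeks". Taking five working days per week, 4 × 5 = 20 sessions. Visits V2 to V21 number 21 − 2 + 1 = 20. V21 is therefore both the last session and the last scheduled side-effect record, at about week 4. Likewise V2 to V11 is 10 visits, or about 2 weeks.

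**2. What follows V21.** Weeks after the end of treatment: 6 − 4 = 2, 8 − 4 = 4, 16 − 4 = 12, 28 − 4 = 24 and 56 − 4 = 52. Marks in Table 1 at these five visits:

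- side-effect documentation: 0 of 5
- audiometry and speech audiometry: 0 of 5
- TQ, VAS, BDI and SCL-90R: 5 of 5 each

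About 56 − 4 = 52 of 56 weeks, or 52/56 = 93%, carry no scheduled side-effect record or audiometry.

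**3. What can be known about duration, case by case.**

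- *Side effect starts and resolves between V2 and V21.* Onset and end are both recorded to within the spacing of the treatment visits. Duration can be quantified.
- *Side effect present at V21.* Onset is recorded and the end is not. Duration is right-censored: it is at least the time from onset to V21.
- *Physical side effect starting after V21.* No scheduled record of onset or end.
- *Worsening of tinnitus or mood after V21.* Visible on the TQ, VAS, BDI and SCL-90R at the follow-up visits, to within the visit spacing.

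**4. Audiometry.** There are two measurements after baseline.

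- *Changed at V11, back to baseline at V21.* Duration is bounded by the interval from V1 to V21. This is the only pattern with an upper bound.
- *Changed at V11 and still at V21.* Minimum of about 2 weeks, no upper bound.
- *First changed at V21.* Onset lies between V11 and V21. There is no later measurement, so nothing is known about persistence.

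**The case against.** **GCP and the condensed format.** Events are documented and handled under GCP, and a journal article need not reproduce the adverse event form. Open events may well be followed to resolution under the full protocol, and a blank cell in Table 1 does not prove that they are dropped. This stands as a caution about actual conduct. It does not remove the mismatch: the article sets out an explicit schedule, states no rule for following open events, and ties the duration analysis to routinely sampled data. Ad hoc follow-up is not routine sampling and need not be equally complete in all three arms.

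**Safety-relevant data do continue.** A reader might infer that nothing bearing on safety is collected at V22 to V26. The documents do not support that. TQ, VAS, BDI and SCL-90R are all marked there. The TQ covers hearing problems, sleep and somatic discomfort (Outcome measures), and the Data sets section says all gathered data serve the safety evaluation, which may refer to patients rather than variables. These scales would show later tinnitus or mood worsening. They do not measure hearing thresholds or local physical effects, and the Safety section does not name them.

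**Censored is not unmeasurable.** A reader might also infer that duration cannot be quantified at all. That goes too far: effects that resolve during treatment can be timed, and those open at V21 have a recorded onset and a lower bound.

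**The stated aim sets no persistence requirement.** This is true. The Objectives ask for audiometric impairment and documentation of side effects, and the schedule supplies both up to the end of treatment. The conflict is with the Data analysis section, which adds duration.

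**Conclusion.** The point holds in limited form. The stated schedule supports duration only for effects that end before V21. For effects open at V21 it gives a minimum, for later physical effects it gives nothing scheduled, and for a hearing change first seen at V21 it gives no repeat measurement.

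The 93% in the check is a share of calendar time. A reader might take it as the share of safety information lost, but the documents give no rate of persistent or late-onset effects, so no impact can be computed. Nor does the share rest on an undisputed length of follow-up: Table 1 labels follow-up as 11 months, while the text runs to week 56.

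The conclusion assumes five sessions per week without gaps, and that Table 1 is the complete schedule, as the Baseline assessments section presents it. If the full protocol already follows open events at the later visits, only the article's table and wording need correcting. This is a worthwhile, inexpensive improvement to a stated aim. It does not touch the primary efficacy analysis.

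**What to change.** 1. Extend the side-effect row of Table 1 to V22 to V26, in all three arms. At each visit record the end date of any event open at V21, and the onset and end of any new event. Add this to the Follow-up assessments section.
2. In the Data analysis section, limit the audiometric claim to change from baseline at 2 and 4 weeks. Report any audiometric change present at V21 as of unknown, censored duration.
3. State that an event not known to have ended is reported as right-censored at the last visit where it was recorded.

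If the follow-up visits cannot be changed, the least that is needed is a sentence saying that all durations are censored at V21.

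The cost is one short block of questions at five visits that already take place, plus two wording changes. Follow-up visits become slightly longer. Dates will rest partly on patient recall, most of all between weeks 28 and 56, where the gap is 56 − 28 = 28 weeks.

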### Randomization

A randomisation list was prepared by the Department of Medical Biometry of University Hospital of Tübingen (RV) using permuted blocks. Allocations were concealed in opaque sealed envelopes, that are opened by a third person immediately prior to the first treatment.

### Treatment

After screening, written informed consent, physical ENT examination and audiological assessments, patients will be assigned to one of the real (SAC, TAC) or sham (PLC) treatment groups. TMS will be applied using a Magstim Super Rapid (The Magstim Company Ltd, Whitland, UK) with a figure-eight coil (diameter of each winding: 70 mm, biphasic stimulus of 250 μs, peak magnetic field: 2T). The individual motor threshold (AMT) will be assessed at the beginning of the first treatment session. AMT is defined as minimum stimulation intensity required to induce a motor evoked potential (MEP) of more than 200 μV on at least 5 out of 10 trials from the contralateral abductor pollicis brevis muscle (APB) while maintaining a voluntary contraction of about 20% of maximum [39]. Stimulation (cTBS) intensity is 80% AMT and will be applied to each side for 40 s in alternating order. Fifteen minutes after the first two trains, a second pair of cTBS will be applied (a total of 2400 stimuli per day). Patients receive cTBS treatment each working day for 4 weeks.

